##### Retention

Retention for the whole study and per group will be defined by the number of participants who complete the final study assessment compared with the number of participants enrolled and randomized. A retention rate of ≥80% (in each group) has been established as our criterion to determine feasibility for a future study.

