#### Secondary Outcomes

##### Overview

Effect size estimates will be evaluated using secondary outcome measures of physical and cognitive function, dual task performance, ADLs, and HRQL, as described in further detail in the following sections. These measures will be assessed at baseline and at 4 and 8 weeks after starting the intervention. See Table 4 for a summary of secondary outcome measures.

**Table 4 table4:** Secondary outcome measures by time point.

Outcome		Assessment measure	Time points

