### Statistical Procedures

#### Sample Size

A sample size of 12 participants per group is considered appropriate for a pilot study to assess feasibility [58], accounting for an estimated attrition rate of approximately 20% in each group. Power calculations were not performed for the secondary outcomes as the primary study purpose is to assess effect estimates for further program development and evaluation in a future RCT.

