#### Data Analysis

Descriptive statistics will be used to summarize recruitment and retention rates, program adherence, participant satisfaction, and safety in both groups. Means and 95% CIs will be reported for the secondary outcomes at baseline, 4 weeks, and 8 weeks within and between groups to derive effect estimates for analysis and sample size calculations for a subsequent larger-scale RCT. Paired 2-tailed *t* tests and 2-tailed *t* tests will be used to compare the changes in the secondary outcome measures over the 8-week study period within and between the 2 randomized groups, respectively. All participants will be included in the analyses based on the intention-to-treat principle according to their group allocation from randomization.

We will explore the contribution of age and sex to feasibility end points and secondary outcomes. Given the modest sample size and importance of age for both cognitive and physical function, we limited our inclusion criteria to the age of ≥50 years to ensure a more homogenous study population. Other important clinical factors such as BMI and medications will be included for descriptive purposes.

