### Data Quality and Management

Our research team is trained in the study processes, measurement protocols, and institutional requirements. We have received peer review comments from the Canadian Lung Association (Multimedia Appendix 1) and incorporated this feedback into the study protocol. Standard operating procedures are in place for all study procedures. The research team will make every effort to have participants complete all study elements, and incomplete or missing data will not be imputed. All participants will be closely supervised by the exercise professional, who will support adherence and accurate data collection.

As per national and institutional research guidelines, all participants will be given a unique study ID to be used in place of their name for all study data. Physical data collection forms and data collected from questionnaires will be kept in a cabinet in the principal investigator’s office under lock and key. Electronic data will be stored on a password-protected research server. Once data collection is complete, deidentified data will be exported to statistical software for analysis.

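### The plan says all participants are analysed by intention to treat, but its t tests on 8-week change, with no imputation, leave out everyone without a week 8 value

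*Protocol article*

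**What the plan says.** All statements are in the protocol article.

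- **Population (Data Analysis):** "All participants will be included in the analyses based on the intention-to-treat principle according to their group allocation from randomization".
- **Method (Data Analysis):** paired and two-sample t tests, both two-tailed. Their stated role: "will be used to compare the changes in the secondary outcome measures over the 8-week study period within and between the 2 randomized groups". Means with 95% CIs are also to be reported at baseline, 4 weeks and 8 weeks, "to derive effect estimates for analysis and sample size calculations for a subsequent larger-scale RCT".
- **Missing data (Data Quality and Management):** "incomplete or missing data will not be imputed".
- **Expected loss (Sample Size):** 12 per group, "accounting for an estimated attrition rate of approximately 20% in each group".
- **Retention (Retention section and Table 3):** counted by completion of the final study assessment. The criterion reads: "A retention rate of ≥80% (in each group) has been established as our criterion to determine feasibility for a future study".
- **Visits (Secondary Outcomes, Overview):** "These measures will be assessed at baseline and at 4 and 8 weeks after starting the intervention". Table 4 shows all three visits for most secondary measures.

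**The concern.** Three statements cannot all hold once anyone misses week 8: that every participant is included, that the test is a t test on 8-week change, and that nothing is imputed. The article fixes all three itself, so this is not a detail left to an unseen analysis plan. It also plans for the loss that triggers the conflict.

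Two things are at stake. First, results could be labelled as covering all randomized participants when they do not. Second, the 8-week change estimates help size the next trial, and they would be distorted if those who leave differ from those who stay. That is plausible here. Only the intervention arm has the cognitive training, about 60 minutes on 5 days a week, or roughly 5 hours a week (Cognitive Training). The Discussion (Study Summary) also notes that patients with cognitive limitations are more likely not to complete rehabilitation, so dropout may be related to the functions being measured.

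**Working it through.** **Inputs from the protocol article.** 12 per group and 24 in total; attrition about 20% in each group (Sample Size); retention criterion of at least 80% per group (Retention); visits at baseline, week 4 and week 8 (Secondary Outcomes). No alpha, power, effect size or SD is given.

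**1. The plan's own figure.** The 12 per group rests on a cited source for pilot studies, so no power formula reproduces it. It does fit an attrition allowance: 9 / (1 − 0.20) = 11.25, rounded up to 12; and 10 × 1.2 = 12. The plan therefore expects about 9 to 10 evaluable participants per arm, not 12.

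**2. Who enters the t tests.** The change is the week 8 value minus the baseline value. If week 8 is missing and not imputed, there is no change score.

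- Per arm: 12 × 0.80 = 9.6 analysed.
- Overall: 24 × 0.80 = 19.2 analysed, and 24 × 0.20 = 4.8 excluded.
- At the retention criterion: 0.80 × 12 = 9.6, so at least 10 of 12 must be retained. An arm can pass with 2 of its 12 excluded.
- Chance that all 24 have week 8 data, assuming independent dropout at 20%: 0.8^24 = 0.0047, about 0.5%.

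**3. Precision.** The 95% CI half-width for the between-group difference, in SDs of change, is t(0.975, 2n − 2) × √(2/n).

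| n per arm | Half-width |
|---|---|
| 12 | 0.85 |
| 10 | 0.94 |
| 9 | 1.00 |

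**4. Possible bias, simple form (the shift is assumed).** If a fraction d of an arm is missing and those people would have changed g SD less than those observed, the observed mean change in that arm is overstated by d × g. With d = 0.20 and g from 0.25 to 1.0, this is 0.05 to 0.20 SD. If only the intervention arm is affected, the between-group difference is overstated by the same amount. If both arms have the same d and g, the between-group bias is 0, but each within-group change is still overstated by 0.05 to 0.20 SD.

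**5. Possible bias, simulated (patterns assumed).** Settings: 12 per arm; no true effect; outcome SD of 1 at each visit; correlations 0.6 (baseline and week 4), 0.6 (baseline and week 8) and 0.7 (weeks 4 and 8). Bias is in outcome SDs.

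| Leave intervention arm | Leave control arm | Bias in the 8-week t test comparison |
|---|---|---|
| 3 with worst week 4 change | 1 at random | 0.22 |
| 2 with worst week 4 change | 2 at random | 0.15 |
| 3, moderately linked to week 4 change | 1 at random | 0.11 |
| 2, moderately linked to week 4 change | 2 at random | 0.08 |
| 2, same mechanism in both arms | 2, same mechanism | 0.00 |

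The trial-to-trial SD of the estimate is about 0.40, so even the largest of these biases is smaller than the sampling noise. A likelihood-type estimate using baseline and week 4 data stayed within 0.02 SD of zero in the scenarios where it was computed. That follows from the set-up, because dropout was made to depend on observed data. It is not evidence about this trial.

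**The case against.** The strongest defence is that the population sentence is mainly about allocation. It ends by referring to the randomized group, and that part is respected: someone who stops training but attends week 8 stays in the assigned arm. Exclusion follows from a missing week 8 value, outcome by outcome, and not from failing to finish the intervention. The primary outcomes are descriptive feasibility measures that do not depend on these tests, and the secondary outcomes are explicitly unpowered. The protocol also commits to every effort to have participants complete all study elements. For 24 participants, a plainly described available-case analysis is defensible. All of this stands. It lowers the seriousness, but it does not make the sentence about including all participants true.

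A reader might infer more than the documents support.

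- **That all efficacy estimates come from completers.** They do not. Week 4 means and CIs can include everyone seen at week 4; only the 8-week change comparisons are restricted.
- **That the trial will show a false benefit of 0.22 SD.** That figure is the top of an assumed range. It uses 3 losses against 1, whereas the plan expects about 20% in each group. It removes exactly the worst week 4 responders from one arm only, which nothing in the document supports. Losing 3 of 12 is 75% retention, so that arm would already miss its feasibility criterion.
- **That the bias must favour the intervention.** Neither its direction nor its size can be derived from the document.

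**Conclusion.** The contradiction holds. As written, the 8-week change t tests are available-case analyses by allocated group, not analyses of all participants. At the expected 20% attrition they omit about 4.8 of 24 randomized participants, and the chance that they omit nobody is about 0.5% if dropouts are independent. They also ignore the week 4 data of those who leave later.

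The consequence for the estimates is uncertain. The between-group bias is 0 if both arms lose people at the same rate by the same mechanism, and about 0.22 SD in the most adverse pattern examined. These figures rest on assumed correlations and dropout patterns. The point is limited to unpowered secondary outcomes in a feasibility pilot, so it should be fixed but is not critical. It matters mainly because these estimates help inform the next trial's sample size.

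**What to change.** **Preferred.** For secondary outcomes measured at baseline, week 4 and week 8, estimate the 8-week between-group difference with a linear mixed model that treats all three visits as outcomes, with arm-by-visit terms, REML and small-sample degrees of freedom. Include every randomized participant with any data, and state the missing-at-random assumption. Nothing is imputed, so the no-imputation rule can stay. Participants with a baseline value only will be included but will add little to the 8-week contrast.

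**If the t tests are kept.** Replace the population sentence with wording such as: *all participants with available data, analysed by allocated group*. Report the number analysed per outcome and arm, and do not describe the result as including all randomized participants.

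**Cost.** The model needs slightly more programming and an explicit missing-at-random assumption that cannot be verified from the data. No new data are needed, because week 4 is already collected. The alternative costs one sentence and a column of denominators, but it leaves any bias from missing week 8 values in place.

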### Data Quality and Management

Our research team is trained in the study processes, measurement protocols, and institutional requirements. We have received peer review comments from the Canadian Lung Association (Multimedia Appendix 1) and incorporated this feedback into the study protocol. Standard operating procedures are in place for all study procedures. The research team will make every effort to have participants complete all study elements, and incomplete or missing data will not be imputed. All participants will be closely supervised by the exercise professional, who will support adherence and accurate data collection.

As per national and institutional research guidelines, all participants will be given a unique study ID to be used in place of their name for all study data. Physical data collection forms and data collected from questionnaires will be kept in a cabinet in the principal investigator’s office under lock and key. Electronic data will be stored on a password-protected research server. Once data collection is complete, deidentified data will be exported to statistical software for analysis.

## Results

Recruitment began in January 2022. It is estimated that the study period will be 30 months long, with data collection to be completed by December 2023. Study results will be submitted for publication in the summer of 2024.

## Discussion

### Study Summary

COPD is associated with several physical and cognitive impairments contributing to limitations in daily activities that often involve the simultaneous performance of a physical (eg, walking) and cognitive (eg, talking) task, known as dual tasking. The benefits of pulmonary rehabilitation in reducing COPD symptoms and improving daily function are well established [21], and it is known to be feasible and effective when delivered remotely in the home environment via telehealth [26,27,31]. However, traditional pulmonary rehabilitation programs typically focus mainly on physical exercise training without addressing cognitive function despite evidence that many patients with COPD have some cognitive limitations, which can contribute to greater functional limitation, increased health care use, and decreased HRQL [6,23]. Patients with COPD with cognitive limitations are also at increased risk of noncompletion of pulmonary rehabilitation [59], suggesting that a better understanding of cognitive limitations and approaches to improve cognition may lead to better adherence and outcomes. However, to date, no studies have examined a pulmonary rehabilitation approach that specifically combines both physical and cognitive training. Therefore, this protocol describes a pilot RCT that is entirely internet based and home based and combines cognitive and physical training in patients with COPD with the aim of further improving daily function and HRQL beyond traditional pulmonary rehabilitation approaches.

### Cognitive Training Mechanisms

Cortical activity is essential for all motor performance, ranging from complex activities to basic ADLs; thus, the benefits derived from cognitive training can be obtained even in those with normal cognition [60]. Cognitive training has been shown to be more effective in those completing a physical exercise intervention as the neural network is primed for neuroplasticity. Thus, cognitive training may be a complementary strategy in conjunction with physical exercise to improve dual tasking in patients with COPD, which is often required during routine daily activities (eg, talking or avoiding obstacles while walking). COPD is associated with impaired dual-tasking performance, manifested as changes in dual task gait properties, including reduced gait speed [12] and increased gait variability [15]. There is also evidence from our group that loss of neural automaticity may be an underlying mechanism contributing to slower gait speed among individuals with COPD [11]. Collectively, these changes suggest that cognitive limitations may arise from increased attentional demands and neural inefficiency, which may contribute to decreased cognitive and physical performance in COPD [17]. Although traditional pulmonary rehabilitation does not appear to improve dual task gait in patients with COPD [15], cognitive training is known to produce distinct benefits on dual task reaction time [61] and has been shown to independently improve measures of functional mobility among healthy older adults [62]. Therefore, the addition of cognitive training may help improve neural efficiency and attentional capacity in patients with COPD, leading to improvements in dual-tasking ability that may translate to better performance in daily activities and HRQL and reduction in the risk of falls.

Clinical practice guidelines established by several leading organizations recommend cognitive training as a strategy to decrease the risk of cognitive decline (World Health Organization; American Academy of Neurology; National Academies of Sciences, Engineering, and Medicine; and Agency for Healthcare Research and Quality) [63-66]. These recommendations were largely established based on strong scientific evidence in the form of meta-analyses showing both near and far transfer effects from cognitive training in older community-dwelling adults, those with mild cognitive impairment, and those with dementia [67-71]. BrainHQ by Posit Science is a computerized cognitive training platform offering game-based exercises that target the speed and accuracy of information processing across the domains of attention, memory, spatial navigation, executive function, and emotional processing. In the largest RCT on cognitive training to date involving 2832 healthy older adults, speed-of-processing training on BrainHQ was found to improve cognitive and functional performance to a greater extent than other forms of memory or reasoning training, which translated to a reduction in risk of impairments in daily activity performance and an increase in reported quality of life that remained at follow-up of 5 to 10 years [72]. BrainHQ training resulted in improved visual processing speed and accuracy, and these improvements were associated with improved balance and smaller decrements in dual task gait speed among older adults [73,74], which has important implications for patients with COPD who are at risk of falls [42]. To our knowledge, this study will be the first to explore BrainHQ cognitive training in a population of individuals with chronic lung disease.

Given the breadth of impairments associated with COPD and the complexity of routine daily activities, the rehabilitation approach described in this paper combining physical exercise with cognitive training targeting attention, memory, executive functioning, and speed of processing may offer the flexibility to further improve daily function and reduce the risk of falls in patients with COPD beyond physical training alone. Notably, the cognitive training modality to be implemented in this study is distinct from the proposed dual task outcome measure, supporting the potential transfer of gains to a variety of daily activities.

### Strengths

There are several strengths to this study. The physical training program and assessments were specifically designed to support feasibility and safety in the home environment. All participants will be provided with exercise training equipment (foot peddler, resistance bands, Fitbit, and pulse oximeter), which will improve safety and accessibility and standardize physical training and assessments. This study is novel as it provides a new approach to remote assessments of aerobic endurance (ie, foot peddler), functional outcomes, and cognitive assessment and training as part of a home-based pulmonary rehabilitation program for patients with COPD [27]. Our protocol may optimize not only accessibility but also outcomes in home-based pulmonary rehabilitation programs. The use of commercially available software programs (Fitbit, Physiotec, and BrainHQ) supports the future clinical translation of this work as these and other similar programs may be used by clinicians and patients looking to integrate cognitive-physical training into pulmonary rehabilitation programs. Furthermore, the chosen cognitive training platform (BrainHQ) has the largest evidence base and, to our knowledge, is the only brain training program that meets all the National Academy of Medicine criteria for cognitive training [29,30]. Our specific cognitive training protocol was designed in consultation with neuropsychology and cognitive science experts to specifically target common areas of deficit among individuals with COPD.

### Limitations

We also acknowledge that there are limitations to the design of this study. Given the small sample size, we will be unable to adjust the analyses for potential confounders such as medications (opiates, sedatives, or corticosteroids) or COPD exacerbations; however, these factors will be tracked throughout the study period to explore their influence on selected outcomes. This study will be conducted entirely remotely, and therefore, we are unable to prospectively measure specific tests of outcomes such as pulmonary function (ie, spirometry) or neural activity (ie, functional near-infrared spectroscopy). However, some of this information will be derived from chart review or will require future study. Furthermore, cognitive assessments will be completed independently at home, and differences in device or screen size (ie, computer vs tablet) may influence the results. Participants who do not have access to a suitable device will be provided with a tablet for the duration of the study. Owing to the nature of the training intervention and internet-based environment, blinding of participants and the exercise professional is not possible, thus creating a risk of bias. Furthermore, most of the physical training measures and intensity will be ascertained through self-report, which may not be as accurate as if they were captured electronically from the training devices.

### Conclusions

A partly supervised, home-based, telehealth cognitive-physical training program may be an accessible intervention to improve cognitive function and further address dual-tasking abilities in people living with COPD. Evaluating the feasibility and effect estimates is a critical first step to inform future clinical trials evaluating this approach and its effects on physical and cognitive function, ADL performance, and HRQL.

## Appendix

Multimedia Appendix 1 Peer review report from the Chronic Obstructive Pulmonary Disease Catalyst Grant Award.

## Abbreviations

ADL: activity of daily living
COPD: chronic obstructive pulmonary disease
Ex-SRES: Exercise Self-Regulatory Efficacy Scale
FEV1: forced expiratory volume in the first second
HRQL: health-related quality of life
MoCA: Montreal Cognitive Assessment
RCT: randomized controlled trial
RPE: Rating of Perceived Exertion
UHN: University Health Network
